### Treatment plan

As per routine practice, patients will be treated with afatinib 40, 30, or 20 mg tablets once daily, as indicated in the approved labels of the drug. Dose reduction will be allowed based on patient tolerability. Drug administration will be continued until disease progression or significant side effects occur. Based on the recommendations of the current guideline,^23^ “beyond‐progression” use is permitted in case of oligo‐progression with appropriate local treatment.

### Data collection

Clinical parameters, survival data, and baseline PD‐L1 expression level data, obtained using 22C3 or SP263 assays, will be collected from medical chart reviews. Tumor response will be assessed using computed tomography which is to be performed at least 8‐week interval of during treatment and evaluated according to the Response Evaluation Criteria in Solid Tumors (RECIST) 1.1.^24^ Positron emission tomography or brain magnetic resonance imaging will be used, when necessary, as per routine practice. For patients in the prospective cohort, molecular profiling using targeted next‐generation sequencing (NGS) will be performed on tumor tissue obtained at diagnosis and plasma samples obtained before the initiation of afatinib. For efficacy evaluation, treatment outcome parameters, including TTF, ORR, DoR, PFS, and OS, will be calculated. Subgroup analysis will be performed with respect to PD‐L1 expression levels and genetic alterations. Possible treatment‐related adverse events (TRAE) during afatinib treatment, including stomatitis, skin reaction, paronychia, diarrhea, and elevated liver enzymes, will be assessed based on the Common Terminology Criteria for Adverse Events (CTCAE Version 5.0).^25^ In addition, information on immune‐related adverse events (irAE), including pneumonitis, colitis, and hepatitis, will be collected to assess possible association between irAE and TRAE.

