## PATIENTS AND METHODS

### Study design

The SPACE study is a retrospective and prospective, observational, multicenter study. Figure 1 shows the flow chart for this study. Our aim is to evaluate the treatment outcomes and safety of afatinib in patients with advanced SCC who progressed after first‐line platinum‐based chemotherapy plus immunotherapy or platinum‐based chemotherapy followed by immunotherapy. We aim to recruit 130 patients, for retrospective and prospective cohorts of 30 and 100 patients, respectively, from four institutes in South Korea from January 2021 to December 2021. The observational period will be 1 year from the time of final registration. This is not a powered study. The minimum sample size has been set at 130 eligible patients to provide meaningful results.

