**FIGURE 1 tca13880-fig-0001:**
[figure not shown]
Study flowchart. DCR, disease control rate; DoR, duration of response; NGS, next‐generation sequencing; ORR, objective response rate; OS, overall survival; PD‐(L) 1, programmed death‐(ligand) 1; PFS, progression‐free survival; SCC, squamous cell carcinoma of the lung; TTF, time to treatment failure

The primary endpoint of this study is the time to treatment failure (TTF), defined as the time from the start of afatinib treatment to the time of treatment discontinuation for any reason, including disease progression, treatment toxicity, and death. The secondary endpoints are the objective response rate (ORR), duration of response (DoR), disease control rate (DCR), PFS, OS, and safety profiles. In addition to these, the difference in treatment outcome parameters with respect to PD‐L1 expression and genetic alterations will be analyzed. This protocol has been approved by the Medical Ethics Committee of the Kyung Hee University Medical Center, Seoul, South Korea, and all participating institutes. As this study involves human participants, all procedures will be performed in accordance with the ethical standards of the Institutional and National Research Committee, and the 1964 Declaration of Helsinki and its later amendments or comparable ethical standards. This study is subject to the supervision and management of the ethics committees of all participating institutes. This study is registered in the Clinical Research Information Service (CRIS, https://cris.nih.go.kr, registration number KCT0005712), the official registration site for clinical trials powered by the Korea Disease Control and Prevention Agency.

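### The afatinib safety definition stops at the last dose and depends on attribution, so possibly related toxicity that first appears afterwards falls outside the safety result

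*Protocol article*

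**What the plan says.** One sentence in the Data collection section of the protocol article defines the afatinib safety data. It covers possibly treatment-related "adverse events (TRAE) during afatinib treatment, including stomatitis, skin reaction, paronychia, diarrhea, and elevated liver enzymes", graded by CTCAE version 5.0. The next sentence adds immune-related adverse events (pneumonitis, colitis, hepatitis), and information on these "will be collected to assess possible association between irAE and TRAE".

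Other places that bear on the point:

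- **Study design, endpoint paragraph:** the secondary endpoints include "PFS, OS, and safety profiles". The primary endpoint, time to treatment failure (TTF), runs to "the time of treatment discontinuation for any reason, including disease progression, treatment toxicity, and death".
- **Treatment plan:** "Drug administration will be continued until disease progression or significant side effects occur".
- **Study design, opening paragraph:** "The observational period will be 1 year from the time of final registration".
- **Data collection, opening sentence:** survival data come from chart review.

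The article does not mention adverse events irrespective of cause, any period after the last dose, the grading of events still open at discontinuation, or the attribution of later deaths.

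**The concern.** The safety sentence sets two limits: a time window (while on afatinib) and a relatedness filter (possibly due to afatinib).

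The window is tied to something that toxicity itself can bring about. If side effects are a reason to stop the drug, the patients with the worst tolerance have the shortest recording period, and it ends when their toxicity is active. Further toxicity in the following days or weeks has no place in the stated definition.

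The filter matters because every patient has already had immunotherapy, there is no control group, and part of the data comes from charts written before the study began. Whether an event was possibly due to afatinib is then a judgement that cannot be checked against a comparator rate, and for some patients it is read back from notes made for another purpose.

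At stake is the rate of severe and fatal toxicity. Safety is one of the study's stated aims, and the Introduction says the results could support afatinib use after chemotherapy and immunotherapy. A capture rule that loses events mainly in one direction would make the drug look better tolerated than it is.

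**Working it through.** The article gives no figure for this point, so there is no calculation to reproduce. The check is to run each type of event through the stated rules.

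1. **Possibly related event that starts and resolves on afatinib.** Inside the safety definition. No problem.
2. **Possibly related event that starts on afatinib and causes it to be stopped.** Also inside, because it arose during treatment. It is a TTF event as well, and the two records can be matched.
3. **Possibly related event that starts on afatinib, is ongoing at the last dose, and later worsens or proves fatal.** The onset is inside. Whether the recorded grade is the one at discontinuation or the later peak is not stated. Two sites could grade the same patient differently and both comply.
4. **Possibly related event that first appears after the last dose.** Outside the stated window. No other section brings it back: TTF has already ended, and the immune-related sentence concerns toxicity attributed to immunotherapy.
5. **Death after the last dose.** Counted in overall survival, since survival is followed to the end of the observational period. No rule classes it as treatment-related or not, so overall survival does not restore it to the safety result.
6. **Severe event on afatinib judged neither afatinib-related nor immune-related.** Not required by either safety sentence. If it leads to stopping, TTF counts it under discontinuation for any reason, but no adverse event record is called for.
7. **Immune-related event.** Collected, with no stated on-treatment limit, for the association analysis.

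Type 4 is a stated exclusion, type 3 an ambiguity, and type 6 the effect of the relatedness filter.

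**How far attribution can be relied on.** The planned cohorts are 30 retrospective and 100 prospective, so 30/130 = 23% of patients finished afatinib before the study began. The Eligibility criteria also place patients already on afatinib at study start in the prospective cohort, so some of their early toxicity will be chart-based too. The article's own examples overlap across the two categories: diarrhea is listed as afatinib-related and colitis as immune-related; elevated liver enzymes as afatinib-related and hepatitis as immune-related. In a patient recently treated with an immune checkpoint inhibitor, the same clinical picture could be entered under either heading. That choice moves the afatinib toxicity rate and also affects the planned association between the two.

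**Direction.** Types 4 and 6, and type 3 if graded at discontinuation, all remove events or lower grades. Nothing in the stated rules adds events to offset this, although the word possible keeps the filter fairly wide.

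**Size.** This would need the share of severe events that first appear or peak after the last dose, and the share judged unrelated. The document gives neither.

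**The case against.** Four objections deserve an answer.

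**Condensed article.** A reporting window after the last dose, follow-up of open events and an attribution field are commonly left to the full protocol or case report form. This stands for pure omissions: silence on open events would not be a finding by itself. It does not cover the window and the filter, which the article states.

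**The restriction is softer than it looks.** A reader might infer that adverse events are recorded only if judged afatinib-related and only during treatment. The text does not support that. It refers to possible relatedness, which is wider than events judged related; its list of toxicities is open; and immune-related events are collected without an on-treatment limit. This stands. Still, events attributed to immunotherapy do not fill the gap for late afatinib toxicity or for severe events of other cause.

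**Worsening and fatal events.** A reader might also infer that an event starting on drug and later becoming severe or fatal is excluded, or that toxicity-driven TTF events cannot be matched to the safety table. Neither follows. Nothing freezes the grade at the last dose, and toxicity that causes stopping arises on drug. What remains is the lack of a rule for the final grade.

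**Related events only is a defensible choice.** In advanced squamous lung cancer, all-cause events mix in disease events, and the study is observational with an approved drug. This is a fair reason not to report all-cause events alone. It is not a reason against recording the severe ones and reporting both rates.

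**Conclusion.** The point holds in limited form. As stated, the afatinib safety data exclude possibly related toxicity that first appears after the last dose, and they leave open the grading of events that continue past it. The relatedness filter makes the reported rate depend on attribution in a setting where attribution is weak.

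The likely effect is under-counting of severe toxicity. Its size is unknown. A reader might want to gauge it by comparing a post-dose window with the median progression-free survival quoted from the pivotal trial. That would not be sound: progression-free survival is not time on drug, treatment beyond progression is allowed in some cases, and the ratio says nothing about how many events fall in the window. Nor does describing afatinib as an irreversible inhibitor show how long toxicity lasts after stopping.

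The conclusion assumes that the safety sentence is applied as written and that the full protocol has no wider rule. Importance is modest: safety is a secondary, descriptive endpoint, the article says the study is not powered, and no decision rule depends on the safety rate. It is worth correcting because the correction is cheap and the likely bias runs one way.

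**What to change.** Revise the safety sentence in the Data collection section so that:

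- adverse events are collected from the first afatinib dose until 30 days after the last dose or the start of the next anticancer therapy, whichever is first;
- for events ongoing at discontinuation, peak grade and outcome are recorded;
- events that are grade 3 or higher, fatal, or lead to discontinuation are recorded whatever their cause, with attribution (afatinib, prior immunotherapy, disease, other) as a separate field;
- the same rule applies to the retrospective and prospective cohorts.

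Report related and all-cause rates side by side. The 30 days is a proposed choice, not a value derived from the article; another short, fixed window would also serve if it is stated and applied uniformly.

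The cost is a wording change, a few added fields on the case report form, and slightly more abstraction from charts already being opened for survival. No new visits or tests are needed. The downside is that some disease-related events will enter the all-cause table, which is why attribution should be kept and both rates shown.

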## MOLECULAR PROFILING USING NGS

Tumor DNA will be extracted from sections (40‐μm thick) of formalin‐fixed, paraffin‐embedded (FFPE) tumor tissue using the QIAamp DNA FFPE Tissue Kit (Qiagen). Plasma will be isolated from 8 ml of whole blood using density gradient centrifugation in Ficoll‐Paque™ PLUS (GE Healthcare). Cell‐free DNA (cfDNA) will be extracted from isolated plasma samples using the QIAamp Circulating Nucleic Acid Kit (Qiagen). The quantity and quality of tumor DNA and cfDNA will be assessed using a 4150 TapeStation System (Agilent) and a Qubit 3.0 fluorometer (Thermo Fisher Scientific), respectively.

Targeted NGS will be performed using Cancer‐PRIME™ (Clinomics Inc.). This panel was designed to characterize single‐nucleotide variants (SNVs), insertion/deletion, and copy number variations in 51 actionable genes. Candidate genes are considered to be included in the cancer panel if they are associated with FDA‐approved therapies or reported clinical trials. The list of genes in this panel is shown in Table 1. The NGS‐based clinical cancer gene assay has been previously published and the assay performance has been validated.^26^, ^27^, ^28^ In brief, 1 μl of purified DNA from each sample will be used to analyze its quality and size using a Bioanalyzer system (Agilent). In addition, DNA concentration will be assessed using the dsDNA BR assay using a Qubit fluorometer (Thermo‐Fisher Scientific). To filter out potential sequencing backgrounds, we will exclude variants that are detected in DNA samples from 30 healthy individuals. Common SNVs obtained from the whole‐genome sequencing data of 50 healthy unrelated Korean individuals will also be excluded.^29^

**TABLE 1 tca13880-tbl-0001:** List of the 51 actionable genes in the cancer‐PRIME™ next‐generation sequencing panel

ABL1	BTK	ERBB3	GNA11	MET	PPARG	TP53
AKT1	CCND1	ERBB4	GNAQ	MTOR	PTCH1	TSC1
ALK	CDK4	ESR1	HRAS	MYCN	PTEN	TSC2
AR	CDK6	FGFR1	IDH1	NOTCH1	RAF1	
BAP1	CDKN2A	FGFR2	IDH2	NRAS	RET	
BRAF	DDR2	FGFR3	KIT	PDGFRA	ROS1	
BRCA1	EGFR	FGFR4	KRAS	PD‐L1	SMO	
BRCA2	ERBB2	FLT3	MAP2K1	PIK3CA	STK11	

## STATISTICAL ANALYSIS

All of the time‐to‐event data on treatment outcome parameters will be estimated using the Kaplan–Meier method. The median value and a two‐sided 95% CI will be described. Univariate and multivariate Cox regression analyses will be performed to estimate the potential clinical parameters or molecular subtypes associated with treatment outcomes.
